### Randomization

Participants will be randomized 1:1 between direct and delayed start (after 18 months) of treatment using an online Interactive Response System (IXRS) tool, stratified for somatostatin analogue use (yes/no) and age (< 40 and ≥ 40 years).

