#### Secondary outcomes

Change in PLD disease severity, assessed by the validated PLD-Q questionnaire, calculated over the first 18 months of the trial and compared between the direct start group (on treatment) and delayed start group (on standard of care).Liver growth rates within individuals compared before treatment and during treatment. In the direct start group, historical growth rates (Fig. 3a, b) will be compared with growth rate during 18 months of treatment (b–e) and in the delayed start group, growth rates during the first 18 months of the trial (untreated, b–c) will be compared with the last 18 months of the trial (treated, c–d).The incidence of (serious) adverse events, compared between the direct and delayed start group in the first 18 months of treatment.

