### Sample size calculation

In our own DIPAK 1 trial [13], the mean liver growth rate in patients meeting the inclusion criteria was + 5.8% ± 2.8% per 18 months. Since the information on liver growth rate in this specific group is scarce, we conservatively doubled the SD to ensure enough power. We aim at fully stopping liver growth. Using β = 80%, α = 0.05, and incorporating a 20% drop-out rate, inclusion of 36 patients is needed to show this effect. In other proof-of-concept studies in PLD, similar numbers of patients were included [28, 29].

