### Questionnaires

Questionnaires will be sent digitally to the patient at screening, 6, 18, 24 and 36 months. Quality of life will be assessed using the SF-36 and BD-II questionnaires, PLD disease severity using the validated PLD-Q questionnaire and menopause related complaints using the MENQOL questionnaire [32, 33].

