### Statistics

#### Statistical analysis

Analyses are performed after completion of the study. For the primary outcome, liver growth during the first 18 months of the trial compared between direct and delayed starters, an unpaired t-test will be used. In case of missing data, last information will be used adjusted for the duration of follow up. For questionnaires, the delta in scores during the first 18 months of the trial will be compared between direct and delayed starters. To compare liver growth within individuals before and during treatment, a paired t-test will be used. Adverse events will be categorized and the number of adverse events per category will be compared between direct and delayed starters using an unpaired t-test.

For all primary and secondary analyses, we will perform pre-defined sensitivity analysis to adjust for age, disease type (ADPKD vs. ADPLD), total liver volume at baseline, total kidney volume at baseline, use of somatostatin analogues, and test differences in treatment effects among these variables (interaction). In a sensitivity analysis we will test for differences in the outcome variables between the first 18 months of the trial and the second 18 months of the trial in the direct start group, using a breakpoint analysis. All analyses will be performed based on an intention to treat principle. As a sensitivity analysis, we will perform a per-protocol analysis.

In an additional analysis we will explore whether liver growth is linear and whether the liver growth rate during treatment is different in the first 6 months of treatment compared to the 12 months thereafter, using a multiple mixed model.

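### The secondary PLD-Q comparison uses the 18-month change with no adjustment for the baseline score: valid, but less precise than ANCOVA on data already collected

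*Protocol article*

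**What the plan says.** The Secondary outcomes section defines the symptom endpoint as "Change in PLD disease severity, assessed by the validated PLD-Q questionnaire, calculated over the first 18 months of the trial", compared between the direct and delayed start groups. The Statistical analysis section repeats the contrast for all questionnaires: "For questionnaires, the delta in scores during the first 18 months of the trial will be compared between direct and delayed starters". It names no test for them, whereas it names a t-test for liver growth, within-patient growth and adverse events.

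For all primary and secondary analyses the same section pre-defines sensitivity analyses that "adjust for age, disease type (ADPKD vs. ADPLD), total liver volume at baseline, total kidney volume at baseline, use of somatostatin analogues". The baseline questionnaire score is not in that list. Randomization is "stratified for somatostatin analogue use (yes/no) and age (< 40 and ≥ 40 years", so symptom score is not a stratification factor.

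A pre-treatment score is available: "Questionnaires will be sent digitally to the patient at screening, 6, 18, 24 and 36 months". (Data collection and management places the first questionnaire at baseline rather than screening. Either is before treatment.)

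**The concern.** Subtracting the baseline score treats month-18 PLD-Q as if it followed baseline with a slope of 1. With equal SDs at the two times, the slope is rho. When rho is below 1 the subtraction over-corrects, so whichever arm happens to start with worse symptoms tends to show the larger improvement. Nothing described in the article removes this. Symptom score is not stratified, and the listed covariates help only as far as they predict baseline PLD-Q.

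PLD-Q is the only symptom-based efficacy measure among the primary and secondary outcomes, and the Perspective section names relief of symptoms as part of the trial's hope. The sample was sized on liver growth alone, so no power is claimed for PLD-Q. What is at stake is avoidable imprecision in the main symptom result of a 36-patient trial.

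**Working it through.** **The plan's own figure.** The only stated sample size is for liver growth. Inputs from Sample size calculation: "the mean liver growth rate in patients meeting the inclusion criteria was + 5.8% ± 2.8% per 18 months"; "we conservatively doubled the SD to ensure enough power", so SD = 2 × 2.8 = 5.6; growth fully stopped, so difference = 5.8; alpha 0.05 (taken as two-sided); 80% power (the article writes it as beta).
- n per arm = 2 × (1.960 + 0.842)² × (5.6/5.8)² = 14.63, rounded up to 15, or 30 in total.
- 20% drop-out: 30 × 1.2 = 36, as stated (30/0.8 = 37.5, rounded up to 38).

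The 36 reproduces. It does not bear on PLD-Q, and this point does not touch it.

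**Inputs for PLD-Q.** "Participants will be randomized 1:1 between direct and delayed start", hence 18 per arm, with 29 evaluable (15/14) as an allowance for drop-out. Rho and the PLD-Q SD are not in the article. Rho is assumed between 0.3 and 0.9, and the SD is taken as equal at both times and set to 1.

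**Variance.**
- Change score, per patient: 2(1 − rho).
- ANCOVA, per patient: 1 − rho².
- Ratio: (1 + rho)/2.

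**Power.** Two-sided noncentral t at 0.05. The effect is fixed where the change-score test has 80% power: 0.961 change-score SDs at 18 per arm, 1.080 with 29 evaluable. ANCOVA on baseline alone loses one degree of freedom, and its variance is multiplied by 1 + 1/(N − 4). With the two stratification factors added and assumed non-prognostic, it loses three, and the multiplier is 1 + 3/(N − 6).

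| rho (assumed) | variance ratio | baseline only, N = 36 | baseline only, N = 29 | baseline + 2 non-prognostic strata, N = 36 |
|---|---|---|---|---|
| 0.3 | 0.65 | 92.8% | 92.5% | 91.0% |
| 0.5 | 0.75 | 88.9% | 88.6% | 86.8% |
| 0.7 | 0.85 | 84.8% | 84.5% | 82.4% |
| 0.8 | 0.90 | 82.8% | 82.4% | 80.2% |
| 0.9 | 0.95 | 80.7% | 80.4% | 78.0% |

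All are to be read against 80% for the change score. If the strata are well balanced between arms, as stratification intends, adding them costs almost nothing: 84.7% instead of 84.8% at rho 0.7, N = 36.

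**Where the lost precision comes from.** Let D be the chance baseline difference between arms in score SDs. Given D, the change-score estimate is shifted by −(1 − rho)D.
- At 18 per arm, D has SD √(2/18) = 0.33. The chance that |D| exceeds 0.3 is 37%, and that it exceeds 0.5 is 13%.
- For D = 0.5 the shift is 0.35, 0.25 and 0.15 SD in size at rho 0.3, 0.5 and 0.7.
- At rho 0.5 the estimator variances are (2/18) × 1.00 = 0.111 for the change score and (2/18) × 0.75 = 0.083 for ANCOVA. The difference, 0.028, equals (0.5 × 0.333)². The shift from imbalance is therefore the whole of the extra variance.

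**Simulation check.** 20,000 trials, 15 per arm, true effect 0.80, rho 0.5. Both methods averaged 0.80. Among trials with D above 0.3, the change score was off by −0.25 and ANCOVA by 0.00. Power was 56% for the change score and 67% for ANCOVA.

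**The case against.** The strongest objection is that the article fixes the endpoint (a change) but names no model for questionnaires, and that a condensed article may leave the model to a full protocol or SAP not shown here. ANCOVA on the change would be compatible with the quoted sentence. The covariate list is also shared by all outcomes, so an outcome-specific baseline might not appear in it. Part of this stands: an unseen SAP may already specify ANCOVA. It does not dispose of the point, because the article states both the contrast and the covariates for adjustment, and as written neither uses the baseline score.

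A reader might infer that the planned comparison is biased. The documents do not support that. Allocation is randomized, so the change score is unbiased over repeated randomization and its type I error is kept. The shift exists only conditionally on the imbalance that occurs. A reader might also count that shift and the wider interval as two separate harms. They are one: the interval for the change score already carries the shift.

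The objection on size also stands in part. Rho is assumed, and the 80% starting power is only a reference point. With two non-prognostic strata in the model the gain at N = 36 is about 2 points at rho 0.7 and essentially gone at 0.8, and at 0.9 the model is 2 points worse than the change score.

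**Conclusion.** The point holds as a matter of efficiency, not validity. With the baseline PLD-Q score as the only covariate, the gain over the change score at 18 per arm is about 13, 9 and 5 points of power at rho 0.3, 0.5 and 0.7, and about 1 point at 0.9. These figures rest on equal SDs at the two times, a linear relation and an assumed rho.

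The point applies to the secondary PLD-Q outcome. SF-36, BD-II and MENQOL are exploratory, so for them it is only an option. It should not be extended to the liver-growth comparison. It is worth settling beforehand because the trial is small and open-label, and a baseline covariate chosen after the data are seen would be open to challenge.

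**What to change.** Replace the questionnaire sentence in Statistical analysis, for PLD-Q, with:

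> The month-18 PLD-Q score (or its change from baseline) will be compared between arms by ANCOVA with the baseline PLD-Q score as covariate.

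The stratification factors (somatostatin analogue use; age below 40 or 40 and over) may be added. Keep the raw change by arm as a descriptive summary. The same model can be used for the exploratory questionnaires. If a SAP already specifies this, aligning the article's wording with it is enough.

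The cost is one sentence and 1 to 3 degrees of freedom, with no new data.

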## Discussion

The AGAINST-PLD study will assess the effect of the GnRH-agonist leuprorelin on liver growth in pre-menopausal patients with severe PLD. If effective, leuprorelin may help to stop disease progression in female PLD patients at risk of rapid disease progression. Ultimately, this may avoid liver transplantations, which is desirable in view of the donor shortage and the procedure related morbidity and mortality [12].

We study the effect of anti-estrogenic therapy in PLD, a novel and promising target, using a broad proof-of-concept approach. To reiterate a recent literature review [22], estrogens have a cyst growth promoting effect and the idea to study estrogen inhibition in female PLD patients has been coined several times [3, 20, 22, 34]. To inhibit the effect of estrogens, several approaches could be used [22]. We chose for a GnRH-agonist, because this is the only way currently available to inhibit all three types of estrogen receptors and also block the effects of other female hormones such as progesterone. For other treatments, such as tamoxifen (a selective estrogen receptor modulator) it is so far unclear whether they would inhibit, stimulate or either have no effect on estrogen receptors in PLD and they would not block other female hormones which possibly also affect liver growth [22].

Since the study treatment ceases the menstruation and can lead to menopause-related complaints, blinding is not possible and as a consequence we adopted a prospective open-label with blinded endpoint assessment (PROBE) design. Randomization between direct and delayed start of treatment makes it possible to compare treated and untreated patients, but also to compare liver growth before and during treatment within patients, and it will render additional safety and tolerability data. Finally, the design meets the urgency felt by patients, stating that they would not participate if they could be in a control group without treatment.

### Efficacy–safety ratio

Leuprorelin blocks the production of all female sex hormones and can have several side effects that we know from menopause, such as hot flushes, night sweats, mood swings, vaginal dryness and disturbed sleep [26]. On the long term, estrogen depletion could increase the risk of osteoporosis and cardiovascular events [35, 36].

We tried to enhance the tolerability and the efficacy-safety ratio of the study medication in several ways. First, only patients with the highest need for new treatment options are included in this study. The target population consist of patients who, despite current treatment options, will mostly need a liver transplantation in the future if the course of the disease cannot be altered. We discussed the design of this trial in a focus group with eight patients meeting the inclusion criteria and with de Dutch Liver Patient Foundation. They felt that the burden of the disease is high and the perspective grim, and most patients thought that the potential of efficacy of a new treatment outweighs side effects.

Second, with the help of patient focus groups we adjusted the study design to the preferences and needs of patients to be included, especially to limit adverse events related to the mechanism of action of GnRH agonists. A potential option to reduce side effects would be to add a low-dose estrogen and/or progesterone as “add-back therapy”, as is used in GnRH agonist treatment for endometriosis [26]. However, because this is a proof-of-concept trial testing whether estrogen depletion curtails liver growth, we decided to not allow add-back therapy. Instead, we added that non-hormonal treatments can be used to treat side effects, such as clonidine in case of hot flushes and venlafaxine in case of mood swings. In addition, also at the request of the patients in the focus group, a gynecologist will be available at all study sites to counsel patients before and during the study, at some sites supported by a trained nurse as “menopause coach”.

On the longer term, estrogen depletion could lead to an increased risk of osteoporosis and a slightly enhanced cardiovascular risk [26, 35, 36]. With a treatment duration of 18 or 36 months, we do not expect large detrimental effects on the long term. However, to ensure optimal safety, patients with a history of cardiovascular disease and a low bone-density at screening will be excluded from the trial and during the trial blood pressure, cholesterol levels and bone-density will be monitored (Fig. 4). In addition, all patients will receive advise on healthy food intake and calcium and vitamin D supplementation.

### Interim analysis

To safeguard a favorable efficacy–safety ratio during the trial, a Data Safety and Monitoring Board will meet regularly to discuss the progress and interim results. A formal interim analysis for safety and futility will be performed when 50% of the patients (n = 18) have reached 18 months, the time point at which the primary outcome is assessed.

### Perspective

In case the trial is positive, leuprorelin treatment will at first be especially indicated in patients suffering from severe, symptomatic PLD given the nature of the intervention and the expected side-effects. However, when more experience is gained, and leuprorelin also shows a good efficacy–safety ratio in a real life setting, the use of this drug could be extended to patients with less severe forms of PLD, that notwithstanding are symptomatic.

With the AGAINST-PLD study, we venture outside the somatostatin analogue era and explore a promising new target for intervention to stop PLD progression: inhibition of female sex hormones. In this trial we will include patients with the highest need for treatment. In this way we hope to be able to reduce liver growth, and associated symptoms, an urgent unmet need in PLD.

## Data Availability

De-identified individual participant data collected during the trial will be made available upon request to researchers who provide a methodologically sound proposal and whose use of the data has been approved by the AGAINST-PLD Steering Committee.

## Abbreviations

ADPKD: Autosomal Dominant Polycystic Kidney Disease
ADPLD: Autosomal Dominant Polycystic Liver Disease
AMH: Anti Mullerian Hormone
BD-II: Beck Depression Inventory Questionnaire
CT: Computed tomography
DEXA: Dual Energy X-ray Absorptiometry
DIPAK: Developing Intervention strategies to halt Progression of Autosomal Dominant Polycystic Kidney Disease
ER: Estrogen receptor
FSH: Follicle stimulating hormone
GnRH: Gonadotropin receptor hormone
GPER: G-coupled protein estrogen receptor
LH: Luteinizing hormone
MENQOL: Menopause Specific Quality of Life
MRI: Magnetic resonance imaging
PLD: Polycystic liver disease
PLD-Q: Polycystic Liver Disease Questionnaire
PROBE: Prospective open label study with blinded endpoint assessment
